**Main research objective**

The main objective of this study is to test the *null hypothesis that the use of a chatbot such as Vitalk over a period of eight weeks does not result in different mental health outcomes in a treatment and control group* of health workers in Malawi. The null hypothesis will be tested in a two-arm RCT comparing the pre-treatment to post treatment scores using standardized scales for depression, anxiety, resilience, and burnout.

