**Sampling method**

Study participants will be recruited from all primary, secondary and tertiary care facilities within Blantyre district on a first come-first served basis. While this is a convenience sample based on self-selection, random assignment to treatment and control groups will counteract biases inherent to this approach. All participants are volunteers and agree to be assigned to either the treatment or the control group.

The required study population size for paired tests of correlated means was calculated using STATA 17 and is based on the following:

- Pre-post-treatment difference of 1.5 points on standard test scales
- Standard deviation of the difference = 6
- Power 80%
- Significance level 5%

This results in a minimum of 128 participants per study arm. Given the continuity experience – the proportion of participants completing the pre- and post-treatment assessments for depression, anxiety and stress – of 20-45% reported by Daley, Hungerbuehler et al. (2020), we assume that the dropout rate will be as high as 75% for at least one of the standard mental health assessments. This means that a sample of 512 participants will be required per study arm to yield an effective post intervention sample of 128. Furthermore, if 20% of potential study participants will not meet inclusion criteria or drop out for other reasons, about 640 people will need to be recruited initially per study arm. Therefore, the total number of participants for this study is 1280.

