**Data analysis method**

Data analysis will begin after the final workshop is concluded . There will be no interim sharing or analysis of trial data other than monitoring sample size in the two treatment arms and data completeness and appropriateness per data analysis plan for the entire trial data set. Data monitoring will be done by the trial manager.

The data analysis will start with descriptive statistics and bivariable analyses for mental health outcomes, resilience-building behaviors, intermediate outcomes, and user and study characteristics (non-modifiable and modifiable factors). This will include tests for central tendency and distribution.

The difference between treatment and control arms in mental health outcome scores at baseline, mid-study check-in and end-of-study-will be calculated using a linear, mixed-effect model for longitudinal data (e.g., STATA *mixed* or SPSS *MIXED*) applying maximum likelihood estimation, which takes into account any time trends. This method will allow the simultaneous modelling across different time points and estimate the difference in outcomes between the treatment and control groups across the entire study period.

This study will utilize Interpretative Phenomenological Analysis (IPA) as the main method of analysis for the qualitative data that shall be collected during the focus group discussions. Content Analysis will also be utilized to evaluate the participants’ experience in relation to pertinent social and psychological theories in order to explain attitudes and stigma behaviors. This process will also help to identify solutions and interventions that can be applied in order to ensure increased willingness to properly support health workers facing mental health challenges and a reduction in stigma against mental illness.

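### The mixed model's target contrast is not pinned down: read literally it is a whole-period arm difference that includes the pre-treatment baseline, which would dilute the effect

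*Combined protocol and SAP*

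**What the plan says.** The quantitative effectiveness analysis is one paragraph under Data analysis method. It begins: "The difference between treatment and control arms in mental health outcome scores at baseline, mid-study check-in and end-of-study-will be calculated", using a linear mixed-effects model fitted by maximum likelihood. It says that the method allows for trends over time and models the time points together. The aim it then gives is to "estimate the difference in outcomes between the treatment and control groups across the entire study period". There is no model equation, arm-by-time term, primary visit, baseline covariate or constraint on the baseline means.

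The Main research objective describes a two-arm trial "comparing the pre-treatment to post treatment scores using standardized scales for depression, anxiety, resilience, and burnout". Section 4.1 places the first assessment before treatment, the middle one at weeks 4-5 and the last at week 9. Under Sampling method, the size rests on a paired test with these inputs: "Pre-post-treatment difference of 1.5 points on standard test scales" and "Standard deviation of the difference = 6", with 80% power and a 5% level.

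**The concern.** Baseline is measured before either intervention starts. Under Study period, the tests are taken at the opening workshop and the link to the allocated platform follows by email. Randomisation therefore makes the expected arm difference at that visit zero. If the whole-period difference is fitted as one arm coefficient with baseline among the outcomes, a known zero is averaged into the estimate and the effect shrinks.

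Maximum likelihood also keeps participants who have only a baseline score. The plan allows for dropout of up to 75%, so such records could outnumber the complete ones and pull the coefficient further towards zero. A real week-9 effect could then be reported as small or absent. Allowing for a time trend does not prevent this, because a common trend is not the same as an arm effect that differs by visit.

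An analyst who instead fits arm-by-time terms gets an undiluted answer from the same data. As written, the choice between the two could be made after the results are known.

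**Working it through.** **The plan's own figure.** Paired test, two-sided 5%, 80% power, difference 1.5, SD 6. Normal approximation: (1.960 + 0.842)² × (6/1.5)² = 125.6, so 126. The exact noncentral t gives 128 (power 0.80), so "This results in a minimum of 128 participants per study arm" reproduces. Then 128/0.25 = 512 per arm, 512/0.80 = 640, and 2 × 640 = 1280.

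**Inputs for the comparison**
- From the plan: 1.5 points, SD of change 6, three visits, 128 completers out of 512 per arm.
- Assumed: the 1.5 is a between-arm effect at week 9 (the plan uses it as a pre-post difference); compound symmetry with correlation ρ = 0.3, 0.5 or 0.7; true effects at the three visits of 0, 0.75, 1.5 (linear growth) or 0, 1.5, 1.5 (full effect by mid-study); 1:1 arms and equal missingness in both.
- The SD of change fixes the score variance: σ² = 36 / [2(1 − ρ)], so σ = 5.07, 6.00 and 7.75.
- Power is 1 − Φ(1.96 − effect/SE).

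**A. One arm coefficient, 128 complete per arm.** The expected estimate is the mean over visits: (0 + 0.75 + 1.5)/3 = 0.75, or (0 + 1.5 + 1.5)/3 = 1.00. SE = σ√[(1 + 2ρ)/3] × √(2/128). At ρ = 0.5: 6 × 0.816 × 0.125 = 0.612. Power is 23% for 0.75 and 37% for 1.00.

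**B. Arm-by-time, unconstrained change contrast at week 9.** Expected estimate 1.5; SE = 6 × 0.125 = 0.750; power 52% at every ρ.

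**C. Arm-by-time, baseline means constrained equal, week-9 contrast.** Expected estimate 1.5; SE = σ√(1 − ρ²) × 0.125. At ρ = 0.5: 6 × 0.866 × 0.125 = 0.650; power 64%.

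**With dropout: 128 complete and 384 baseline only per arm.** In model A a complete record carries weight 3/(1 + 2ρ) and a baseline-only record carries weight 1, so the expected estimate is

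128(d₁ + d₂)/(1 + 2ρ) ÷ [128 × 3/(1 + 2ρ) + 384] = (d₁ + d₂)/(6 + 6ρ),

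where d₁ and d₂ are the mid-study and week-9 effects. At ρ = 0.5 this is 2.25/9 = 0.25 or 3/9 = 0.33. SE = √[2 × 36/(192 + 384)] = 0.354.

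| Model | Expected estimate | Power at ρ = 0.5 | Power over ρ 0.3-0.7 |
|---|---|---|---|
| *128 complete per arm* | | | |
| A, linear growth | 0.75 | 23% | 14-37% |
| A, full by mid-study | 1.00 | 37% | 21-58% |
| B | 1.5 | 52% | 52% |
| C | 1.5 | 64% | 58-70% |
| *384 of 512 baseline only* | | | |
| A, linear growth | 0.22-0.29 | 11% | 7-17% |
| A, full by mid-study | 0.29-0.38 | 16% | 9-27% |
| B | 1.5 | 60% | 56-64% |
| C | 1.5 | 64% | 58-70% |

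If half of each arm of 512 stays to mid-study and a quarter to week 9, model A gives 0.31-0.56, still well below 1.5. C has the highest power in every scenario run.

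**The case against.** The strongest reply is that the plan nowhere says a single pooled coefficient will be fitted. The sentence introducing the model lists the difference at each of the three visits, which reads naturally as visit-specific contrasts. The main objective is a pre-to-post comparison, which may be taken as the contrast the model is meant to deliver. An arm-by-time model fits this wording and dilutes nothing. That stands: a reader might infer that the plan commits to a diluted estimate, and the text does not support that.

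A reader might also infer that the plan throws away the baseline by treating it as an outcome. It does not follow. In an arm-by-time model a baseline kept among the outcomes still contributes its information, and the constrained model recommended here keeps it there too. Only the single-coefficient fit misuses it.

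Nor does the single coefficient always have the least power. At correlation 0.3 with complete data and full effect by mid-study it has 58%, against 52% for the unconstrained change contrast, although its estimate is still 1.00 rather than 1.5.

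Finally, a longitudinal target is not foreign to the plan, since specific objective 3 concerns episodes during the study. That supports a post-baseline average as a secondary summary. It does not justify including the pre-treatment visit. Nor does the ambiguity settle the matter in the plan's favour, because the visit-specific reading still leaves the primary visit unnamed.

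**Conclusion.** The analysis model and its target are under-specified, and the one summary target stated, taken literally, includes the pre-treatment visit and departs from the main objective. Dilution is a conditional finding: it occurs if one arm coefficient is fitted. In that case a 1.5-point week-9 effect has an expected estimate of 0.75-1.00 with complete data, that is 50-67% of its size. With 384 of 512 per arm contributing baseline only, it is about 0.22-0.38, or 15-26%.

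These sizes rest on the assumed trajectories, compound symmetry, correlations of 0.3-0.7 and the use of 1.5 as a between-arm effect. The dropout figures further assume that everyone lost leaves straight after baseline, which the plan does not say. That even the best contrast reaches only 64% at correlation 0.5 partly reflects a separate matter: 128 was sized for a within-arm paired test, whereas a between-arm difference in change of 1.5 with SD 6 needs 252 per arm. The ranking of C above A and B held in every scenario run.

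**What to change.** Rewrite the model paragraph to state:

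1. Time is categorical (baseline, week 4-5, week 9).
2. Arm-by-time terms are included, with baseline means constrained equal between arms. Alternatively, baseline is a covariate and only the two later visits are outcomes.
3. The within-participant covariance is unstructured.
4. The primary contrast is the arm difference at week 9, which matches the main objective. The week 4-5 difference is secondary.
5. The whole-period difference is removed as the target.

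The cost is one paragraph, settled before the data are analysed. The visits, data and STATA or SPSS mixed procedure stay the same. The small downside is that a single-visit contrast gives up an overall summary; an average over the two post-baseline visits can be kept as a secondary result.

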**Risks**

Vitalk is not intended to replace a mental health professional or to offer treatment. Users are made aware of this in the informed consent that each participant is required to sign. Study participants are advised to seek additional support if they show a high risk of depression, anxiety, or stress during the study. Where Vitalk identifies a risk issue, the user is sent details of support services, including the national suicide line, and, if the participant elects the option, a follow up conversation with a healthcare professional from Vitalk who is not affiliated with the study is initiated. Participants identified as high risk or with suicidal tendencies will be removed from the study and referred for mental health support. Under no circumstances will the participant’s identity be shared with the research team or anybody outside this study.

The Vitalk App, the mental health resource website and all literature and presentations shared with the research participants shall contain contact information of mental health service providers that the research participants may access in the event of needing further psychological support.

We expect minimal risks to study participants due to COVID-19. The risk of exposure that may be encountered during the workshops is significantly mitigated by the fact that the majority of health workers are vaccinated against COVID-19. Regardless of this, both the research team and participants will be required to maintain the recommended amount of social distance, wear face masks and follow local guidelines as stipulated by the ministry of health.

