Originating from Brazil, Vitalk is an automated chatbot delivering mental health content to its users using a conversational format, with the aim of improving well-being by reducing stress, anxiety and depression using a preventative approach to mental health (Daley, Hungerbuehler et al., 2020). The Vitalk app uses psychoeducation, cognitive restructuring, behavioral activation, gratitude, and practical exercises (such as breathing, relaxation and meditation) to bring about improvements in users’ mental health (ibid). These techniques and strategies are rooted in CBT and Positive Psychology, two commonly used psychotherapy methodologies that have been used widely in various settings and have registered high effectiveness among patients presenting with various psychological challenges (Beck, 2011; Seligman, 1998; Wills, 2009). Only the treatment arm of the study will have access to Vitalk.

- - 1. Mental health resource website (control group, *passive*)

The control arm of the study will have access to a website with links to mental health resources from WHO and other self-help providers as well as contact information for psychologists and mental health counselors in Malawi. This website consists of a few pages with basic mental health and coping information, links to mental wellbeing resources, mood meter and standardized mental health tests. Its content is static without user interaction beyond clicks to access web-based
[figure not shown]
mental health resources. Whether or not these resources are used depends entirely on the initiative of control group participants.

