To achieve some degree of participant blinding to the intervention NO information about Vitalk or specifics about interventions in the treatment and control groups will be shared with workshop participants. Participants who completed registration will NOT be informed of their admission into the trial during the workshop; this will happen through an email after the workshop that provides the links to either Vitalk for the treatment group or the website for the control group or informs those not eligible for the trial. The trial manager will monitor whether the desired sample size is achieved; if it is not, additional recruitment efforts and workshops may be necessary.

Participants in the treatment group will receive daily messages and counseling for the first four weeks of the trial to encourage engagement with Viki, the Vitalk virtual counselor. This will change to every other day during weeks five though eight. Participants in the treatment and control group will receive weekly emails throughout the trial to encourage use of web mental health resources. Both groups will be asked to use the mood meter at least once a week to monitor mood changes. Those self-identifying with extreme negative emotions will be offered to take a relevant standard test again and encouraged to seek professional help.

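### Participants who become high risk are removed after randomisation, with no stated trigger, follow-up or analysis rule; this may bias the comparison, plausibly but not certainly toward Vitalk

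*Combined protocol and SAP*

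**What the plan says.** **Removal.** The Risks section states that "Participants identified as high risk or with suicidal tendencies will be removed from the study and referred for mental health support". It gives no threshold, instrument, assessor or arm. Section 4.1 places random assignment at registration, and the Study period section excludes anyone severe or suicidal on the initial tests. Removals during the trial are therefore largely people who worsened after assignment.

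**Other text on the same people or on neighbouring groups.** Risks also says "Study participants are advised to seek additional support if they show a high risk of depression, anxiety, or stress during the study". Study period, on the mood meter, says "Those self-identifying with extreme negative emotions will be offered to take a relevant standard test again and encouraged to seek professional help" and does not mention removal.

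**Detection.** Risks says "Where Vitalk identifies a risk issue, the user is sent details of support services, including the national suicide line" and has no matching sentence for the control website. On access: "Only the treatment arm of the study will have access to Vitalk". On contact: "Participants in the treatment group will receive daily messages and counseling for the first four weeks of the trial", then every other day in weeks five to eight. For both arms: "Participants in the treatment and control group will receive weekly emails throughout the trial to encourage use of web mental health resources". The control website is described this way: "Its content is static without user interaction beyond clicks". It does carry a mood meter and the standard tests. Both groups are asked to use the mood meter at least weekly, and all participants are asked to repeat the tests in week 4 or 5.

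**Analysis.** The Data analysis method section names a linear mixed-effects model, fitted by maximum likelihood, over baseline, mid-study and end of study. It states no analysis set, no handling of removed participants and no sensitivity analysis. The list of collected data in Annex 1.2.3 has no entry for removal or referral.

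**The concern.** Removal depends on depression, anxiety or suicidality, the domain that the trial measures. If it also ends outcome collection, the week 9 mean in each arm describes only those who did not become high risk. When the arms remove different shares of such people, the difference in means shifts without any treatment effect.

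A maximum-likelihood mixed model protects against this only when the loss can be explained by data in the model. A removal decided from a recorded GAD-7 or PHQ-9 score that stays in the dataset meets that condition. A removal decided from conversation content that never enters the dataset does not. The plan leaves open which of these applies.

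Two further things are at stake. Specific objective 3 counts the number and duration of clinical episodes, and removal would cut that count short. Removals are also safety information, and nothing in the plan requires them to be reported by arm.

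**Working it through.** **The plan's own figure.** Sampling method gives a difference of 1.5, SD of the difference 6, 80% power and 5% significance. The normal approximation is (6 × (1.960 + 0.842) / 1.5)² = 125.6, so 126. The paired t calculation (two-sided) gives 128, with power 80.2%. Then 128/0.25 = 512, 512/0.80 = 640 and 2 × 640 = 1280. The plan's figures reproduce. They concern precision and do not bear on this bias, but they supply the yardstick of 1.5 points and the SD of 6.

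**Assumptions, not in the documents.** A share q of participants would be high risk without any effect: 2%, 5% or 10%. The probability that such a person is detected and removed is 90% in the Vitalk arm and 90%, 50% or 20% in control. Higher scores are worse. A negative bias favours Vitalk.

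**Step 1: completers only.** Change is taken as normal with SD 6, and the high-risk group is the upper share q.
- Mean of the high-risk group with no effect: m = 6φ(z)/q. For q = 5%, m = 6 × 0.1031/0.05 = 12.38.
- Mean of those retained when a share d of the high-risk group is removed: −dqm/(1 − dq).
- Vitalk, d = 0.9: −0.045 × 12.38/0.955 = −0.58.
- Control, d = 0.5: −0.025 × 12.38/0.975 = −0.32.
- Bias: −0.58 + 0.32, which is −0.27 before rounding.

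| High-risk share | Control detection | Bias, no true effect | Bias, true effect −1.5 |
|---|---|---|---|
| 2% | 90% | 0 | +0.11 |
| 2% | 50% | −0.12 | −0.01 |
| 2% | 20% | −0.21 | −0.09 |
| 5% | 90% | 0 | +0.22 |
| 5% | 50% | −0.27 | −0.05 |
| 5% | 20% | −0.46 | −0.24 |
| 10% | 90% | 0 | +0.33 |
| 10% | 50% | −0.49 | −0.15 |
| 10% | 20% | −0.83 | −0.49 |

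With equal detection and a true benefit, control loses more of its worst cases, so the bias runs against Vitalk.

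**Step 2: the planned type of model.** Large-sample simulation of three visits, within-person correlation 0.5 (assumed), maximum likelihood, scores before removal kept.

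| Trigger | True effect | High-risk share | Control detection | Bias |
|---|---|---|---|---|
| Recorded week 4-5 score | 0 or −1.5 | 5-10% | 90%, 50% or 20% | about 0 (within 0.03) |
| Unrecorded later state | 0 | 5% / 10% | 50% | −0.19 / −0.35 |
| Unrecorded later state | 0 | 5% / 10% | 20% | −0.33 / −0.58 |
| Unrecorded later state | −1.5 | 5% / 10% | 90% | +0.13 / +0.24 |
| Unrecorded later state | −1.5 | 5% / 10% | 50% | −0.03 / −0.10 |
| Unrecorded later state | −1.5 | 5% / 10% | 20% | −0.17 / −0.32 |

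Against 1.5 points, 0.19 to 0.58 is 13% to 39%.

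**The case against.** The strongest reply is that the documents do not establish a bias toward Vitalk, and much of that reply stands.

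- **Deletion.** A reader might infer that the worst outcomes are deleted. No text says so. Loss of later scores is a fair reading of removal from the study. The fate of earlier scores is not stated, and the planned model can use them.
- **Detection.** A reader might infer that detection is known to be more intensive in the Vitalk arm. The mood meter, the offered retest and the week 4-5 tests are common to both arms. The removal sentence names no arm, and Vitalk is also the name of the developer that builds the study portal. The extra in-app route is a reasonable inference from the access, contact and risk-identification text, but it remains an inference.
- **Trigger.** A reader might infer that removal follows chat or mood-meter signals outside the modelled scores. The trigger is undefined, and since extreme mood leads to an offered standard test, a recorded score is possible. The bias is then about zero if that score is kept.
- **Conflict.** The texts can be read as steps: extreme mood, retest, then removal and referral if risk is high. Advice to seek support is compatible with referral. What remains is that the threshold and signal are undefined and the passages do not say how they fit together.
- **Numbers.** All removal rates are assumed. If exactly the worst scorers go, 5% against 1% gives 0.49 points, 10% against 2% gives 0.87, and 3% against 1% only 0.26. These are upper-end illustrations that compare raw means and use the SD of the difference. Exclusion of severe cases at entry may keep removals few.

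The reply does not supply an analysis rule. The benign case needs a recorded trigger and retained data, and the plan promises neither.

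**Conclusion.** The point holds as a design and analysis defect. The protocol states a removal rule that acts after randomisation and depends on the outcome domain, and it says nothing on follow-up, retained data or analysis for those removed.

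The size is uncertain. Under the planned model it ranges from about zero (recorded trigger, earlier data kept) to about 0.2-0.6 points toward Vitalk (unrecorded trigger, unequal detection, no true effect, high-risk share 5-10%). With equal detection and a true benefit, completers show about 0.1-0.3 points against Vitalk. All of this rests on assumed high-risk shares and detection probabilities, SD 6 and a within-person correlation of 0.5.

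The direction is plausibly toward Vitalk, with moderate confidence. The documents do not support calling it certain. The same remedy serves either direction, and it should be in place before enrolment because scores never collected cannot be recovered.

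**What to change.** Leave referral and care unchanged. The sponsor should reconcile the Risks and Study period sections on who is removed and on what signal; this review takes no position on that rule.

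Whatever the rule, separate it from outcome follow-up:

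1. Analyse every randomised participant by assigned arm.
2. Retain all scores recorded up to and including any test that triggered removal.
3. Where consent is not withdrawn, still send the week 4-5 and week 9 scales.
4. Record the date and detection route of each removal, and report removals by arm and route.
5. Add one sensitivity analysis that gives removed participants without later scores an unfavourable value, such as their own worst score or the severe-band cut-off. For the RS-14, unfavourable means low.

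The cost is protocol and consent wording and up to two automated questionnaire links for what should be a small number of people. Some will decline, so the sensitivity analysis is still needed.
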